**Stanford Regulating Circuits of the Brain Study- MDMA (RBRAIN-MDMA): study protocol for a double-blinded, within-subjects, placebo-and-baseline-controlled randomized mechanistic trial of acute MDMA administration**

## **1. Objectives**

- 1.1 Primary objective:** To characterize in depth the acute neural, behavioral, and experiential profile induced by MDMA during conscious and nonconscious processing of positive and negative emotions, and to examine how these profiles vary as a function of baseline stratification based on circuit profiles.
- 1.2 Secondary objective:** To characterize in depth the acute neural, behavioral, and experiential profile induced by MDMA during cognitive processing, monetary reward processing, and naturalistic resting-state, and to examine how this profile varies as a function of baseline stratification based on circuit profiles.

## **2. Methods**

### **2.1 Trial design and overview**

A mechanistic clinical MDMA trial to investigate the effects of MDMA on human brain circuit function using a double-blinded, within-subjects, placebo-and-baseline-controlled randomized design. The design includes four testing sessions including baseline, placebo, 80mg MDMA hydrochloride (HCl), and 120mg MDMA HCl, randomized within subjects.

### **2.2 Study setting and personnel**

Data will be collected at Stanford University in Stanford, CA. Eligibility surveys will be collected through REDCap in the participant's native environment. Screening visits will be conducted at the Stanford Clinical and Translational Research Unit (CTRU), a research clinic located on the Stanford Campus. Baseline and drug visits will be conducted at the Stanford Center for Cognitive and Neurobiological Imaging (CNI), a human magnetic resonance imaging (MRI) facility dedicated to research.

In-person screening procedures will be conducted by trained medical professionals including phlebotomists (blood draw), research nurses (ECG and vital signs), trained research coordinators (drug and psychiatric histories), and licensed study clinicians (physical examinations). Baseline and drug visit procedures will be conducted by trained research coordinators (study assessments and scanning) and licensed study clinicians (drug administration, monitoring, and safety assessments). These procedures are not part of standard care or intended as an intervention.

### **2.3 Informed consent**

Informed consent procedures will be conducted by a trained research coordinator during screening visits. The research coordinator thoroughly explains the study protocol and answers the participant's questions before consent is obtained.

### **2.4 Additional consent provisions for collection and use of participant data and biological specimens**

During consent, study participants are informed that information from analyses of their coded samples and their coded medical information will be put into one of the National Institutes of Health (NIH) databases, along with information from the other research participants, and will be used for future research. Saliva samples are collected at multiple timepoints during drug visits for hormone analysis. A participant may opt-out of saliva collection for analysis during consent. The decision to withhold consent for saliva sampling collection will not determine a participant's eligibility to be in the study.

## **2.5 Interventions**

### *2.5.1 Intervention description*

After baseline visit, each participant will receive placebo, 80mg MDMA HCl, and 120mg MDMA HCl in a randomized order. Given the within-subjects design of the study, each participant will receive all three of the specified doses across the duration of the trial. Drug visits will be scheduled 10-14 days apart to avoid drug carry-over effects. Participants will arrive fasted for drug visits in the morning to reduce the risk of emesis. They will complete a urine drug screen and pregnancy test (if applicable) and have their baseline vitals recorded at the Stanford Center for Cognitive and Neurobiological Imaging, where they will be met by the study clinician. Participants will be instructed to orally ingest pills with water or an electrolyte solution. For safety reasons, pulse, blood pressure, temperature, and oxygen saturation will be monitored and recorded every 30 minutes throughout the drug visit. The total visit time for drug visits will be 6-8 hours.

## **2.6 Randomization and blinding**

### *2.6.1 Sequence generation*

Participants will be randomly assigned a dose order (80mg MDMA HCl, 120mg MDMA HCl, and placebo), and each participant will receive all three doses.

### *2.6.2 Concealment mechanism*

With our analysis plan and recruitment goal informing the number of randomization assignments, we will use randomization.com to create a random order dose assignment (80mg, 120mg, and placebo) for each of the 40 study IDs. Study IDs are sequential, starting with 001 and ending with 040.

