### *2.6.3 Implementation*

Unblinded study personnel are responsible for generating the random dose assignments. None of the blinded study staff had access to the subject ID dose assignments at any point in the randomization process. Participants are considered to be enrolled in the study once they have finished the in-person screening visit and met all the criteria. After successful enrollment, the participant is assigned a study ID, with the first participant enrolled assigned 001, the second 002 and so on. MDMA and placebo pills were obtained from the Multidisciplinary Association for Psychedelic Studies (MAPS). Before a study visit

involving drug administration, the unblinded study personnel will reference the subject ID and the visit number on the randomization assignment document to make the dose determination. For example, if subject 001 is scheduled for their second drug visit, the unblinded personnel would reference the randomization assignment document for 001, look for their assigned dose for the second drug visit, and count pills according to the information on the assignment. The drug will be delivered to the blinded research team with a label stating the subject ID and visit number.

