## **2.10 Recruitment and Study Cohort**

Healthy volunteers who report  $\geq 2$  uses of MDMA when they were 18 years or older, recruited to attain 4 sessions of data during functional brain imaging. A total of 40 participants will be recruited, equal

numbers of males and females will be recruited. Participants will be recruited through Facebook Ads using IRB-approved material. Individuals who express interest in the study will be directed to an online screening survey in REDCap. Completed screening surveys will be reviewed by research coordinators trained on the study protocol. Surveys will collect information about demographics, psychiatric diagnoses, substance use, and MRI compatibility. Individuals that are eligible by the criteria included in the screening survey will be contacted by a research coordinator to schedule a phone call. On this phone call, research coordinators will give the individuals additional information about the study and collect additional demographic information. Eligible individuals at this point will be consented by a research coordinator and will schedule an in-person screening visit at a research clinic to fully determine eligibility. The following procedures and assessments will be performed at the screening visit: ECG, physical examination, blood draw, vital signs, weight, urine drug test, pregnancy test (if applicable), Hamilton Anxiety Rating Scale (HAM-A), Hamilton Depression Rating Scale (HAM-D), the Mini International Neuropsychiatric Interview (MINI).

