## **5. Statistical methods**

### **5.1 Statistical methods for primary outcomes**

To assess MDMA-induced acute changes in the regional circuit scores derived from the conscious and nonconscious FEET task, repeated measures linear mixed-effects models (LMMs) will be applied. Each outcome measure will serve as the dependent variable, with Dose (placebo, 80mg MDMA and 120mg MDMA) as a within-subjects fixed effect. Further, to assess whether baseline neural profile could predict distinct MDMA-induced acute changes, a median split approach to stratify participants into the high and low activity or connectivity groups and examine the modulation effect of the group. A separate LMM with Dose and Subgroup and their interaction as fixed effects will be implemented. We will focus on the between-subgroup difference between placebo and 120mg MDMA, as well as between placebo and 80mg MDMA. The inclusion of the 80mg dose enhances understanding of dose-dependent MDMA-induced effects and improves blinding. Covariates will include age, biological sex, and motion parameters if they are found to associate with outcomes. For our primary analysis on the pre-registered circuit measures, we will not perform multiple comparison correction as they measure overlapping constructs and do not meet strict criteria for independent measures. We acknowledge the issue of multiple measures, as the detailed set of assessments may measure overlapping constructs and may not meet strict criteria for independence. An alternative approach involves identifying measures that show significant MDMA-induced effects using a  $p < 0.05$  threshold, examining the correlations among these effects, and selecting the measures with the greatest MDMA-induced effect sizes. Additionally, we propose an exploratory option of using principal component analysis (PCA) to form components from correlated measures to reduce dimensions of our data.

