### **5.3 Interim analyses**

We plan the power of our study to be able to detect a small effect of MDMA on brain activation. However, recent studies have shown that this effect can be in the medium range in tasks similar to the ones we have adopted. Therefore, we will run interim analyses to determine if our effects of interest can already be detected when we collect N = 17 participants.

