### **5.4 Methods for additional analyses (e.g., subgroup analyses)**

A further novel aspect of our project will be to examine sex as a biological variable as a potential moderator of MDMA-induced effects on experience, behavior, and brain function. In healthy humans, biological sex has been implicated in the subjective and physiological impact of MDMA, although the data on these effects is very limited. The acute psychoactive effects of MDMA have been reported as more pronounced in women than in men. On the other hand, men report higher blood pressure effects on MDMA than women. To our knowledge, sex differences in the acute impact of MDMA on human neural circuit function have not been investigated.

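### The protocol states no balancing of the six dose orders, overall or by sex; the likely cost is some precision, not bias, and blocking by sex plus a visit term would recover it

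*Protocol*

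**What the plan says.** Section 2.6.1 gives the method in one line: "Participants will be randomly assigned a dose order (80mg MDMA HCl, 120mg MDMA HCl, and placebo"), with every participant receiving all three. Section 2.6.2 adds that a web tool will be used to "create a random order dose assignment (80mg, 120mg, and placebo) for each of the 40 study IDs". Section 2.6.3 attaches IDs to people by order of enrolment, "with the first participant enrolled assigned 001, the second 002 and so on". None of the three sections mentions blocks, a Latin square, equal use of the orders, or a stratum.

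Section 2.10 states that "A total of 40 participants will be recruited", with equal "numbers of males and females will be recruited". Section 5.4 plans to "examine sex as a biological variable as a potential moderator of MDMA-induced effects".

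The primary mixed model in section 5.1 is specified "with Dose (placebo, 80mg MDMA and 120mg MDMA) as a within-subjects fixed effect". A second model adds the baseline subgroup and its interaction with dose. The possible covariates are age, sex and motion; visit number is not among them. Section 5.3 plans an interim look "when we collect N = 17 participants".

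**The concern.** Three conditions over three visits give six orders. Allocating them in blocks makes each dose fall at each visit almost equally often. Drawing an order at random for each ID leaves that balance to chance, and chance balance is poor at 40 participants and proportionally poorer at 20 per sex.

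Visit position could matter here because the same scanner tasks and computerised tests are repeated at baseline and at all three drug visits, so practice or habituation is plausible. If responses drift over visits and the model has no visit term, the drift goes partly into the realised dose contrast and partly into the residual.

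Sequence generation is protocol content with its own section here, and the list must exist before the first dose. A later analysis plan can add a model term but cannot rebalance doses already given.

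**Working it through.** The protocol gives no balance or power figure on this point, so there is nothing of its own to reproduce.

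**Inputs.** 40 participants (2.10); 20 per sex if recruitment is equal (2.10); 17 at the interim (5.3); 3! = 6 orders (2.6.1). Assumed: each ID draws one of the six orders independently with probability 1/6.

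**Dose-by-visit counts, n = 40.**
- Expected count 40/3 = 13.3; SD = √(40 × 1/3 × 2/3) = 2.98.
- Over 200,000 simulated lists, the largest departure from 13.3 among the nine counts is at least 3 in 85%, at least 4 in 65% and at least 5 in 44%. The median smallest and largest counts are 9 and 18.
- The best possible split of orders (7, 7, 7, 7, 6, 6) has probability 15 × 40!/(7!⁴ × 6!²)/6⁴⁰ = 0.0027.

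**Within one sex, n = 20.** Expected count 6.7, SD 2.11. In 55% of lists some dose sits at one visit position for at least half of that sex, against 17% at n = 40.

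**Difference in mean visit position, 120 mg minus placebo.** For one participant the difference is ±1 in four of the six orders and ±2 in two, so its variance is (4/6) × 1 + (2/6) × 4 = 2.

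| Set | Formula | SD (visits) |
|---|---|---|
| All 40 | √(2/40) | 0.22 |
| One sex, 20 | √(2/20) | 0.32 |
| Men minus women | √(2/20 + 2/20) | 0.45 |
| Interim, 17 | √(2/17) | 0.34 |

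**Precision without a visit term.** Assume outcome SD 1, within-subject correlation ρ = 0.5 and linear drift b per visit. The paired difference has variance 2(1 − ρ) = 1 from noise plus 2b² from random order. The SD of the estimate is √((1 + 2b²)/40):
- b = 0: √(1/40) = 0.158
- b = 0.25: √(1.125/40) = 0.168
- b = 0.5: √(1.5/40) = 0.194

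With blocks the estimate's SD stays at about 0.16 at both drifts. The relative variance cost without blocks is 2b²/[2(1 − ρ)], so it depends on ρ. At b = 0.25 it is 0.125/1 = 12.5% for ρ = 0.5, 0.125/1.4 = 9% for ρ = 0.3, and 0.125/0.6 = 21% for ρ = 0.7.

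**Precision with a visit term.** Simulated variance inflation of the 120 mg minus placebo contrast, relative to perfect balance:

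| n | Mean | 95th percentile |
|---|---|---|
| 40 | 1.03 | 1.08 |
| 20 | 1.06 | 1.17 to 1.19 |

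**After blocking.** At n = 40 every count is 12 to 14 and the position difference is at most 0.075 visits. At n = 20, blocked within sex, every count is 6 to 8 and the difference is at most 0.15.

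**The case against.** Four points on the other side carry weight.

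- **Independence is inferred.** A reader might conclude that the protocol rejects balancing. It does not; it is silent. The settings of the web tool are not described, and a block option cannot be excluded. Every simulated figure above depends on the independent reading.
- **Inference stays valid.** A reader might also infer that the dose effect is biased, or that a sex difference would be an artefact of dose order. The documents do not support that. Under random orders, unmodelled drift enters the within-subject residual, so the standard error already covers it. Simulated type I error without a visit term was 4.8% to 5.4% at n = 40 and n = 20 for drifts of 0.1 to 0.5 SD per visit, and 4.9% to 5.1% for the male–female comparison.
- **Blocking alone gains little in the reported analysis.** With blocks but no visit term, the reported standard error stays near 0.167 at a drift of 0.25 although the true SD is about 0.16. The test becomes conservative: about 3.9%, and about 1.7% at a drift of 0.5. The gain appears only if visit is also modelled.
- **Carry-over and sex.** The protocol spaces drug visits 10 to 14 days apart to avoid carry-over, and nothing here quantifies an effect of the preceding dose, so no claim is made on that. The sex comparison is an additional analysis, not the primary contrast.

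All four stand. They limit the harm to lost precision; they do not remove the imbalance.

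**Conclusion.** The concern holds as a minor, inexpensive improvement to precision. On the natural reading of sections 2.6.1 to 2.6.3, noticeable imbalance of dose over visits is likely: about 85% of lists have a count off by 3 or more. In proportional terms it is worse within each sex.

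If visit is left out of the model, the cost is an estimate SD of 0.17 to 0.19 instead of about 0.16, under an assumed drift of 0.25 to 0.5 SD per visit and a within-subject correlation of 0.5. With no drift there is no such cost. If visit is modelled, the average variance cost is about 3% overall and 6% within a sex. In the worst 5% of lists it is at least 8% overall and at least 17% to 19% within a sex.

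There is no bias on average and no inflation of type I error. The conclusion falls away if the list was in fact generated with balanced orders.

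**What to change.** 1. State in section 2.6.1 how the orders are generated. If a balanced option was already used, say so; only the visit term in step 3 then remains.
2. Otherwise have the unblinded staff generate the list, or its unused part if enrolment has begun, in permuted blocks of the six orders separately for men and women. With 20 per sex this is three full blocks plus two further orders (3 × 6 + 2 = 20). The two sexes' remainders can be chosen to complement each other.
3. Add visit (first, second or third drug visit) as a fixed effect in the section 5.1 models, and hence in the similar models of section 5.2, so that the standard error reflects the balance.

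The cost is a few minutes of list generation and a short amendment. There are two drawbacks. IDs would need two ranges by sex in place of the single 001 to 040 order. Block size would also have to stay out of anything the blinded team sees: section 8.2 sends important amendments to study staff and participants, so the amendment should say that the orders are balanced within sex and leave the block details in a file held only by the unblinded staff.

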### *2.6.3 Implementation*

Unblinded study personnel are responsible for generating the random dose assignments. None of the blinded study staff had access to the subject ID dose assignments at any point in the randomization process. Participants are considered to be enrolled in the study once they have finished the in-person screening visit and met all the criteria. After successful enrollment, the participant is assigned a study ID, with the first participant enrolled assigned 001, the second 002 and so on. MDMA and placebo pills were obtained from the Multidisciplinary Association for Psychedelic Studies (MAPS). Before a study visit

involving drug administration, the unblinded study personnel will reference the subject ID and the visit number on the randomization assignment document to make the dose determination. For example, if subject 001 is scheduled for their second drug visit, the unblinded personnel would reference the randomization assignment document for 001, look for their assigned dose for the second drug visit, and count pills according to the information on the assignment. The drug will be delivered to the blinded research team with a label stating the subject ID and visit number.

#### *2.6.4 Blinded personnel*

The study design is double blind, both the participant and the research team, including study clinicians, are blinded to the dose assignment. Blinded research staff includes clinical research coordinators, study clinicians, research nurses, and scanning personnel. All data collection is conducted by the blinded research team. Data analysts for both the interim analysis and the final analysis are unblinded.

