#### *2.11.7 Data management*

The following data management and quality control procedures will be implemented. All study data will be entered into computerized data files utilizing: (1) Microsoft Access for data entry on recruitment and testing schedule tracking; (2) REDCap survey software for real-time entry and verification of data from self-report instruments during assessment visits. All the data entry systems will employ automatic, real-time range, logic, and missing value checks. Data sets will be cleaned, verified, and archived, and then read into R (<https://www.r-project.org/>) or equivalent data analytics software, which also will be archived. One official copy of all the study data and a master data dictionary will be maintained and updated regularly by the study data analyst. All analytic and tracking database files will be stored in a secure Stanford network drive with daily backups. One copy of the backups will be saved on-site and one off-site. Separate archival databases will be permanently maintained. For the protection of human subjects' confidentiality, unique anonymous study IDs will be used for data storing, tracking, and reporting. The data files can be shared by authorized study personnel both on-site and in remote locations via a secure virtual private network. Data security will be ensured through industry-standard password protection and data encryption. Brain imaging data are evaluated at the time of acquisition for any observable abnormalities that require a clinical radiological report, to exclude neurological abnormalities. We transfer data from the scanner acquisition site to the project database via anonymized ID from a secure server (Flywheel). The imported raw scan files (called "NIfTI" files) are visually inspected by the experienced postdoctoral researcher overseen by [name], prior to analysis. The files are run through a sophisticated quality control pipeline that checks for factors such as the extent of whole-brain coverage, the quality of motion correction, image registration, and parameter maps. Anonymized data will be kept in a structured file system that includes selected intermediate steps to permit the easy recalculation of data for specific analyses, using the virtual computing environment overseen by the Stanford Neurosciences Institute. Off-site backups of data are kept in a secure facility.

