### 3.2 Brain Imaging Preprocessing

All participants' data will be quantified using the Stanford Et Cere Image Processing System protocol. An fMRI preprocessing pipeline will be completed using SPM8 (<https://www.fil.ion.ucl.ac.uk/spm/software/spm8/>) and FSL 5.0.9 (<https://fsl.fmrib.ox.ac.uk/fsl>) following previously established procedures, including realignment, co-registration, normalization to the standard Montréal Neurological Institute space, and smoothing with a Gaussian kernel of 8 mm full width at half maximum. A participant's data will be included if no more than 25% of time points (38 out of 151 frames) will be censored by frame-wise displacement  $\geq 0.3\text{mm}$  or scaled signal intensity differences  $\geq 10$ . A temporal mask will then be created for each censored volume and its subsequent volume, and will be used as nuisance regressors in the participant-level modeling. Additional quality control diagnostics include visual inspection of the raw fMRI time series for artifacts and signal dropout.

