### **5.5 Methods in analysis to handle protocol non-adherence and any statistical methods to handle missing data**

Expert researchers will visually inspect all the scans and exclude any that cannot be analyzed due to data acquisition errors or artifacts. FMRI scans with critical motion will also be excluded. In our mixed effects models, we will include all available data for each timepoint.

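### Analysts are unblinded, visual scan exclusions are not required to be made blind to dose, and post-dose motion enters the group models only if it is associated with the outcome

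*Protocol*

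**What the plan says.** **Blinding.** Protocol 2.6.4 says that "both the participant and the research team, including study clinicians, are blinded to the dose assignment". It adds: "Blinded research staff includes clinical research coordinators, study clinicians, research nurses, and scanning personnel". It then states: "Data analysts for both the interim analysis and the final analysis are unblinded". Under 2.6.5, two unblinded people hold the randomization list and are kept out of data collection. Nothing is said about keeping them out of image quality control.

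**Scan exclusion.** Section 5.5: "Expert researchers will visually inspect all the scans and exclude any that cannot be analyzed due to data acquisition errors or artifacts". It continues: "FMRI scans with critical motion will also be excluded", with no threshold and no cross-reference. Section 2.11.7 says that the raw scan files "are visually inspected by the experienced postdoctoral researcher" before analysis. Section 3.2 gives a numeric rule: "A participant's data will be included if no more than 25% of time points (38 out of 151 frames) will be censored", where censoring is triggered by framewise displacement of at least 0.3 mm or a scaled signal intensity difference of at least 10. The same section adds visual inspection of the raw time series, without criteria.

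**Covariates.** Section 5.1: "Covariates will include age, biological sex, and motion parameters if they are found to associate with outcomes". Section 5.2 repeats the sentence for secondary outcomes. Neither gives a test, a threshold or a model for judging association.

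**Interim.** Section 5.3 plans an interim analysis at 17 participants, out of the 40 to be recruited under 2.10.

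**The concern.** Two judgement steps come before the Dose estimate: which scans are discarded by eye, and whether motion is in the model. The protocol requires neither to be settled without knowledge of dose, and the second is settled by looking at the outcome data.

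The interim sharpens the first step. Unblinded analysts may see dose effects at 17 participants while scans from 40 − 17 = 23 participants are still to be collected and inspected.

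On the second step, motion at a drug visit is recorded during the scan and so after dosing. MDMA may change it. A model without motion estimates the total effect of dose on the circuit score; a model with motion estimates the effect at a given level of motion. If the choice is made separately for each measure, the primary results may mix the two quantities. Section 5.1 applies no multiplicity correction to the primary circuit measures, so nothing downstream absorbs this flexibility.

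**Working it through.** **1. The plan's own figure.** The only number in the protocol that bears on this point is the censoring limit in 3.2. 0.25 × 151 = 37.75, which rounds to 38 (38/151 = 25.2%). The figure reproduces. The motion limit is numeric, so the discretion lies in the visual step and in the undefined critical motion of 5.5.

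**2. Who is blinded.** Set side by side, 2.6.4 names four blinded roles and declares the analysts unblinded. Sections 2.11.7 and 5.5 name a postdoctoral researcher and expert researchers as inspectors. Neither inspecting role is on the blinded list, and neither is described as unblinded. No sentence bars an unblinded analyst from inspecting scans.

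**3. Visual exclusion, worst case (assumed rate).** The protocol gives no exclusion rate. Suppose 3 of 40 scans at one dose (7.5%) were all dropped from one tail of a normal outcome. The mean of the remaining 37 shifts by φ(−1.44)/(1 − 0.075) = 0.153 SD. That is the shift in one dose mean. With correlation ρ between a participant's repeated scores, the paired contrast shifts by about 0.153 × (1 − ρ), which is about 0.08 SD at an assumed ρ of 0.5.

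**4. Adjusting or not adjusting for motion (assumed range).** The gap between the two Dose estimates is (dose effect on motion) × (slope of outcome on motion). For a dose effect on motion of 0.3 to 0.8 SD and a slope of 0.2 to 0.4, the gap runs from 0.3 × 0.2 = 0.06 SD to 0.8 × 0.4 = 0.32 SD. If the slope is zero, the two estimates target the same quantity.

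**5. The conditional rule itself (simulation).** Set-up: 40 participants, three doses, a within-participant estimator standing in for the mixed model, and 6,000 runs per scenario. Motion enters only if its within-participant association with the outcome has p < 0.05. There is no direct effect of dose on the outcome. Where dose raises motion, it does so by 0.4 SD at 80 mg and 0.8 SD at 120 mg. All of these values are assumptions. Rejection rates at the 0.05 level for 120 mg against placebo:

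| Scenario | Never adjust | Conditional rule | Smaller p of the two fits |
|---|---|---|---|
| (a) Motion unrelated to dose and outcome | 0.050 | 0.049 | 0.053 |
| (b) Dose raises motion; motion unrelated to outcome | 0.050 | 0.046 | 0.069 |
| (c) Dose raises motion; motion and outcome share a within-visit cause (loading 0.6) | 0.049 | 0.219 | 0.266 |
| (d) Dose raises motion; motion contaminates the outcome (slope 0.3) | 0.178 | 0.053 | 0.200 |

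Monte Carlo error near 0.05 is √(0.05 × 0.95/6000) = 0.003. In (c) the rule selects motion in 87% of runs and biases the estimate by −0.26 SD. This is close to the −0.36 × 0.8 = −0.29 expected under constant adjustment, where 0.36 = 0.6 × 0.6. In (d) the unadjusted estimate is off by 0.24 SD (0.3 × 0.8) if the target is the effect that does not pass through motion. If the target is the total effect, that 0.24 SD is part of it. So even calling it an error depends on a target that the protocol has not fixed.

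**6. Age and sex.** Both are constant within a participant, so including or omitting them hardly moves a within-participant Dose contrast.

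**The case against.** A reader might infer that people outside the blinded team discard the scans. The protocol does not say so. Section 2.6.4 calls the research team blinded, its list of roles is introduced as inclusive rather than complete, and the inspectors are not identified with the data analysts. What can be said is that their status is not stated and that unblinded analysts are not barred from the task.

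A reader might also infer that exclusion is entirely by eye, or that the trial's dose effects rest on these choices. Neither is supported. Section 3.2 sets numeric motion limits, 2.11.7 places the raw-file check before analysis and adds a quality-control pipeline, and 5.5 confines visual exclusion to scans that cannot be analysed. Inspectors of raw files do not yet have the circuit score, so selecting on its tail, as the 0.153 SD figure assumes, is a bound and not an expectation.

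Motion is also handled at the first level already, through censoring regressors (3.2) and six realignment parameters (3.4). The 0.06 to 0.32 SD range is the gap between adjusting and not adjusting; it is not bias produced by the conditional rule. The rule helps in scenario (d), and its harm in (c) needs an assumed shared cause. The covariate sentence can also be read as making only motion conditional.

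Finally, coded datasets and locked exclusion lists often belong in a statistical analysis plan, which was not available here, and openly declaring analysts unblinded is not a contradiction.

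All of this narrows the point, but three things remain that the protocol itself fixes: analysts are unblinded at both analyses, discretionary exclusions carry no blinding requirement, and motion adjustment depends on the outcome data. That the conditional rule can help or harm is a reason to decide on motion in advance.

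**Conclusion.** The point holds in limited form and should be corrected, with medium confidence. The exposure is confined to discretionary visual exclusions and outcome-dependent motion adjustment at group level. Its size cannot be derived from the protocol, which gives no exclusion rate, no effect of dose on motion and no relation of motion to the circuit scores. Under the stated assumptions, one-tailed exclusion of 3 of 40 scans moves one dose mean by at most 0.15 SD and a paired contrast by about half that. The conditional motion rule leaves the false-positive rate at about 0.05 when motion is unrelated to the outcome, and otherwise moves it up (0.049 to 0.219) or down (0.178 to 0.053). Section 5.3 says the trial is planned for a small effect but gives no figure, so these shifts cannot be set against a stated target. Independently of any assumed number, the Dose estimates for different circuit measures may not answer the same question.

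**What to change.** 1. **Sections 2.6.4 and 5.5.** Require visual quality control and scan exclusions to be made under coded visits by staff blind to dose. Lock the exclusion list before the dose key reaches the analysts, both at the 17-participant interim and at the final analysis. The two key-holders in 2.6.5 can hold the visit codes. In 5.5, refer critical motion back to the numeric limits in 3.2.

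2. **Sections 5.1 and 5.2.** Replace the conditional clause with one covariate set fixed in advance for all measures. One workable choice is age and sex in every model and no group-level motion term in the primary model, since motion is already handled at first level. The primary estimate is then the total dose effect. Add mean framewise displacement for every imaging measure as a sensitivity analysis and report both results for each measure.

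The cost is a coding step in the data transfer, a few sentences of text and slightly later release of the dose key. Visits and sample size do not change.
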